### Randomisation and blinding

Eligible participants will be randomised after consenting to the study and completion of the baseline assessment. Allocation will follow 1:1 block randomisation, carried out by the study coordinator, using a validated online tool (https://www.sealedenvelope.com/). The study coordinator will be unblinded to treatment allocation and will inform participants of the outcome of the randomisation. Research workers who lead the baseline and follow-up assessments will be blinded to group allocation, but participants and therapists delivering the therapy will not be (it is not possible to blind them to whether the therapy is delivered or received). Participants will be reminded not to discuss their allocation with research workers when they meet them for the assessment. Breaches in blindness will be monitored and recorded and where operationally feasible assessments will be allocated to another (blinded) research worker.

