### Analysis

A sample size of n=20 per randomised group (n=40) will be sufficient to estimate a recruitment rate of 50% with a 95% CI of 34.51% to 65.9% and a retention rate of 80% with a 95% CI of 67.6% to 94.4% (PASS Software 2019). This sample size of 20 per arm will be sufficient to estimate the variability of the primary outcome measure (ie, changes in PSYRATS-AH and O-AS at post-treatment) for future sample size calculations, with 12 per arm sufficient for estimation of the variability for the purpose of sample size calculations.^47^ Difference between groups and 95% CI for the difference will be reported to aid sample size calculations for a definitive trial.

A complete statistical analysis will be drafted prior to recruitment beginning and finalised before any analysis is conducted. There will not be interim analyses or formal stopping rules in relation to this study as the primary goal is to establish feasibility parameters for a definitive trial. Data will be reported in accordance with the CONSORT principles, with the 2018 extension for reporting social and psychological intervention trials.^45^ We note recent CONSORT-SPI guidance, which recommends minimising the distinction between primary and secondary outcomes; therefore, all outcomes will be reported at the end of the trial.^48^ The feasibility data analysis and quantitative data analysis will be carried out by the MHRCT senior statistician clinical trials unit statistician and quality checked by a trial statistician.

Descriptive statistics will be used to summarise feasibility measures (ie, recruitment and retention, uptake of treatment, data completion) overall and by allocated group. Based on the ‘traffic light system/STOP-AMEND-GO’,^49^ progression criteria related to key feasibility outcomes such as recruitment, retention and treatment uptake rates have been proposed. Each criterion has ‘stop/amend/go’ indicators. For example, the progression criterion for treatment uptake will be 75% and above indicates the progression criterion has been met, 51–75% indicates the need to amend and below 50% indicates stop.

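### The stop/amend/go bands for treatment uptake put 75% in two bands and 50% in none, and both results can occur with the planned 20 therapy participants

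*Protocol article*

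**What the plan says.** The Analysis section of the protocol article adopts a stop/amend/go scheme for key feasibility outcomes, naming recruitment, retention and treatment uptake. It then gives numbers for uptake only, as an example: "75% and above indicates the progression criterion has been met, 51–75% indicates the need to amend and below 50% indicates stop".

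The same section sets the planned size: "A sample size of n=20 per randomised group (n=40" in total). The section on randomisation and blinding gives the ratio: "Allocation will follow 1:1 block randomisation". The planned therapy arm is therefore 20 people.

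The article does not say how treatment uptake is calculated. The nearest measure is in Table 1 (Objectives), which lists the proportion of consenting participants in the therapy condition who attend enough sessions to count as exposed. Table 1 does not call this uptake. Nothing elsewhere in the article restates the bands or says how a result on a boundary is to be classed.

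**The concern.** A stop/amend/go rule is useful only if each possible result leads to one verdict fixed in advance. Here the go and amend bands share an end point, and there is a gap between amend and stop. With a small denominator the observed percentage moves in large steps, so it can land exactly on a boundary.

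What is at stake is the reading of one feasibility criterion at its two thresholds: go against amend at 75%, and amend against stop at 50%. No estimate, confidence interval or sample size depends on it.

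**Working it through.** There is no calculated figure in the plan to reproduce, because the bands are chosen thresholds. The check is whether they cover every possible result exactly once.

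**Inputs**
- Go: uptake ≥ 75% ("75% and above indicates the progression criterion has been met").
- Amend: 51% ≤ uptake ≤ 75% ("51–75% indicates the need to amend").
- Stop: uptake < 50% ("below 50% indicates stop").
- Denominator: n = 20, from the planned arm size and 1:1 allocation. That uptake is measured in the therapy arm is an assumption.
- True uptake: not given in the article, so a range is assumed.

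**Step 1: bands as worded.** 75% satisfies both ≥ 75% and ≤ 75%, so it is go and amend. A value u with 50% ≤ u < 51% satisfies none of the three conditions.

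**Step 2: every result out of 20.** Results move in steps of 1/20 = 5 percentage points.

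| Number out of 20 | Uptake | Verdict as worded |
|---|---|---|
| 0–9 | 0–45% | stop |
| 10 | 50% | none |
| 11–14 | 55–70% | amend |
| 15 | 75% | go and amend |
| 16–20 | 80–100% | go |

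Of the 21 possible results, 19 are clear and two are not. Rounding does not help, because 10/20 and 15/20 are exact percentages.

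**Step 3: other denominators.** Exactly 75% needs n divisible by 4, and exactly 50% needs n even. For n up to 40, nothing else falls in the gap: the next result above one half is at least 0.5 + 1/(2n), which is 51.25% or more at n = 40.
- n = 16, 20, 24 or 40: both boundary values can occur.
- n = 18 or 22: only 50% can occur.
- n = 17, 19 or 21: neither can occur.

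**Step 4: how often a boundary is hit with n = 20.** P(X = k) = C(20, k) p^k (1 − p)^(20 − k). Two worked cases:
- P(X = 15) at p = 0.75: 15504 × 0.75^15 × 0.25^5 = 0.202.
- P(X = 10) at p = 0.50: 184756 / 2^20 = 184756 / 1048576 = 0.176.

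| Assumed true uptake | P(exactly 15/20) | P(exactly 10/20) | Either |
|---|---|---|---|
| 50% | 1.5% | 17.6% | 19.1% |
| 60% | 7.5% | 11.7% | 19.2% |
| 70% | 17.9% | 3.1% | 21.0% |
| 75% | 20.2% | 1.0% | 21.2% |
| 80% | 17.5% | 0.2% | 17.7% |
| 85% | 10.3% | <0.1% | 10.3% |
| 90% | 3.2% | <0.1% | 3.2% |

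The chance of an unclear result is roughly one in five for the tabulated true rates from 50% to 80%, and falls quickly above that.

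**The case against.** The strongest reply is that this is loose notation in an illustration. The bands are introduced as an example from a fuller set of criteria that the article does not print. The full protocol may word them cleanly, and the article says that the statistical analysis will be finalised before anything is analysed. At 75%, the go band includes its end point in so many words, so most readers would take 15/20 as go. The final denominator may also not be 20, and at 17, 19 or 21 neither boundary can be hit.

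Much of this stands, and it limits the severity. It does not remove the contradiction: the article states a rule, and the rule as printed gives two answers at one threshold and none at the other. The go reading of 75% is plausible, but the amend band contradicts it. For 50% the wording gives no comparable lead: a stop band that begins below 50% suggests amend, while an amend band that begins at 51% suggests stop.

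A reader might infer more than the text supports.
- *That the progression decision will be made after the data are seen.* That would require the full protocol and the analysis plan to repeat the slip, and neither is shown.
- *That the rule governing the trial's whole purpose is broken.* The Objectives section gives feasibility and acceptability as the primary aim and first efficacy estimates as the second. Uptake is one of at least three progression criteria.
- *That one trial in five would end in an unclear verdict.* This holds only under certain assumed uptake rates and a denominator of 20. At a true uptake of 90% the figure is about 3%.

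**Conclusion.** The uptake bands are wrong as written, with moderate severity. The overlap at 75% and the gap from 50% to just under 51% follow from the text alone and rest on no assumption.

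The practical size does rest on assumptions. With uptake measured in a therapy arm of 20, two of the 21 possible results lack a single verdict. The chance of landing on one of them ranges from about 21% (true uptake 70% to 75%) down to about 3% (true uptake 90%) over the tabulated rates. The article states neither the denominator nor an expected uptake, so these figures show the scale and do not predict the outcome.

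**What to change.** Before any analysis, restate the bands so that they are exclusive and exhaustive, define the uptake denominator, and print the matching counts. Two versions stay close to the present text:

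| Version | Go | Amend | Stop |
|---|---|---|---|
| A: 50% counts as amend | ≥ 75% (15–20 of 20) | 50% to < 75% (10–14) | < 50% (0–9) |
| B: 50% counts as stop | ≥ 75% (15–20 of 20) | > 50% to < 75% (11–14) | ≤ 50% (0–10) |

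Version A keeps the stated go and stop wording but lowers the amend limit from 51% to 50%. Version B suits an intention that 50% should mean stop, and it changes the stop wording. Both take 75% out of the amend band. Either gives each of the 21 results one verdict. The choice belongs to the sponsor and should be recorded in advance.

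The recruitment and retention bands in the full protocol should be checked for the same fault. The cost is one corrected sentence, with no change to design, sample size or data collection. The Trial status section has data collection running to September 2026.

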### Patient and public involvement

The LEAP at the Clinical Psychology and Digital Psychotherapy Department (MHRTC) was convened following the award of the grant supporting the present study. They have been invited to review the protocol, the choice of outcome measures, intervention procedures, recruitment methods and study materials, qualitative interview (format, content and data analysis), and dissemination of research findings. The LEAP has been built to advise on all the stages of the trial.

## Ethics and dissemination

The trial will be conducted in compliance with the principles of the Declaration of Helsinki,^50^ the principles of Good Clinical Practice and in accordance with all applicable regulatory requirements including but not limited to the Research Governance Framework and the Mental Capacity Act.^51^ It has received approval from the Ethics Committee of the Faculty of Psychology (R1/620). If amendments to the protocol are required, the same ethics committee will review them. The Ruhr Universität Bochum is the trial sponsor. The results of the study will be reported and disseminated at international conferences and in open-access peer-reviewed scientific journals. The results will also be available to participants and clinical teams in an accessible format and on the study website.

The study has been prospectively registered with the ISRCTN registry: ISRCTN 35980117. The study is monitored by the Ethics Commission at the Faculty of Psychology (Ruhr-Universität Bochum), and there is an independent Trial Steering Committee (TSC) and Live Experience Advisory Panel (LEAP) also supporting it.

## Trial status

Recruitment to the trial commenced in December 2023 (study protocol V.1.2, dated 24 September 2023) and is planned to finish in April 2025. Data collection is planned to continue until September 2026.
